### Withdrawal

Participants can leave the study at any time for any reason if they wish to do so, without any consequences. If a patient wishes to withdraw during the distractor period, the distractor can be removed in the outpatient clinic and standard treatment will continue. After removal of the distractor, a patient is also free to discontinue participation by refusing to complete questionnaires or follow-up imaging. We do not anticipate any circumstance in which the investigator would recommend the patient withdraws from the study since the potential risks and complications expected are limited and not life-threatening or harmful (see the section “Potential benefits and risks assessment”).

### Data management, monitoring, and publication

Data will be handled confidentially. Data will be administered on an encrypted computer in REDCap: a secured electronic data capture tool for clinical research [31]. Patient data will be anonymized. All included patients are identified by a patient identification number. A list of these numbers with name combinations will be securely stored by the coordinating investigator. The handling of personal data will be performed in compliance with the Dutch Personal Data Protection Act and in compliance with Good Clinical Practice guidelines. Data will be kept for 15 years after the end of the study. Written informed consent from study participants will securely locked away within the hospital.

This study will be monitored by a certified monitor according to the St. Antonius Hospital and Medical Research Ethics Committees United (MEC-U) monitoring policy. Insurance is provided for all participants in accordance with Dutch legislation. The results of this study will be published in peer-reviewed journals and presented at (inter)national conferences. Any protocol amendments will be submitted at the MEC-U for approval and relevant parties, including participants, will be informed if needed.

## Discussion

Joint distraction is a fairly new treatment for patients with CMC1 OA [19]. To our knowledge, to date, 52 patients have been treated with joint distraction. In contrast to other joint distraction treatments, CMC1 distraction is not offered in regular clinical practice yet, only in study context. Distraction therapy can result in less pain and better physical function and can therefore postpone an invasive surgical intervention [12–16, 18]. In a previous study about CMC1 joint distraction, a surgical intervention was postponed for at least 2 years in most (19 of 20) patients (unpublished data).

This trial will test if we can decrease the current distraction duration from 8 to 6 weeks and still achieve sufficient clinical benefits for patients. For knee distraction, a decreased treatment duration of 6 weeks (instead of 8 weeks) resulted in less pin tract infections while good clinical results were still achieved [17, 18]. Therefore, knee distraction is nowadays applied for 6 weeks. It is unknown if 6 weeks of continuous CMC1 joint distraction, compared to 8 weeks, leads to similar results: less adverse events and sufficient clinical benefits (e.g. less pain and better physical function). The outcomes of this study will give a more decisive answer to this question. If safe, the duration of basal thumb joint distraction can be reduced to 6 weeks, reducing patient burden.

This study will also enable to assess the short- and long-term effects of joint distraction in 68 patients. We expect that joint distraction will lead to less pain and better physical function in patients on average, regardless of group. Because this is a relatively new treatment, this trial will provide greater knowledge of potential adverse events. This knowledge allows for more informed decision making for patients considering CMC1 distraction treatment and will help to better define the place of joint distraction in treatment of CMC1 OA.

It is not feasible to blind participants to wearing a distractor for 6 or 8 weeks. Due to logistical constraints, we are also unable to blind surgeons and hand therapists. The lack of blinding might influence our results, but is common in trials assessing a surgical intervention. Besides, we realise the need for additional studies to compare joint distraction with other operative and non-operative techniques. However, we first designed this study to explore the possibilities to decrease distraction duration and bring CMC1 joint distraction, in this regard, in line with other joint distraction techniques. Based on the results of this current study, we will conduct a next comparative study to achieve a better understanding of the effects and benefits of joint distraction directly compared to other techniques (like splinting or trapeziectomy) in the treatment of CMC1 OA.

This study will mainly focus on clinical and patient-reported outcomes. We realise that there is also a need to gain more knowledge about the working mechanism of joint distraction. Future studies can contribute to a better understanding of this mechanism by—for example—focusing on arthroscopic sampling of articular cartilage, detailed imaging techniques, or biochemical analysis of synovial fluids.

There is major evidence that psychosocial factors—such as catastrophic thinking and symptoms of depression and anxiety—account for more of the variation in CMC1 OA symptom intensity than measure of pathophysiology [20, 21, 34]. To study differences in the magnitude of psychosocial factors before and after CMC1 joint distraction, in this study, we will measure symptoms of pain catastrophizing and of depression with two short questionnaires (PHQ-2 and PCS-4) [27, 28]. This could lead to a better understanding of the impact of psychosocial factors on physical function and other outcomes after CMC1 joint distraction therapy. Future studies can focus on exploring other/additional treatment opportunities for patients with CMC1 OA to optimize care (f.e. more effective coping strategies). This could result in a more multidisciplinary approach in treatment of CMC1 OA.

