#### Secondary study parameters

Patient characteristics: gender, age at operation, work status, marital status, and level of highest education.Michigan Hand Outcome Questionnaire (MHQ - Dutch Language Version): a validated 57-item questionnaire that gauges hand health status on a scale from 0 to 100 with higher scores indicating better hand health status [26].Patient Health Questionnaire (PHQ-2): 2-item questionnaire with scores from 0 representing ‘lowest level of depression’ to 6 ‘highest level of depression’ [27].Pain Catastrophizing Scale (PCS-4): 4-item questionnaire rated on a 5-point Likert scale with scores ranging from 0 indicating ‘no catastrophic thinking’ to 16 ‘worst possible catastrophic thinking’ [28].Visual analogue scale (VAS) scores for pain, patient satisfaction, thumb stiffness and function: with scores from 0 representing ‘no pain at all’ or ‘fully satisfied’ or ‘no stiffness at all’ or ‘optimal function’ to 100 ‘worst pain possible’ or ‘not at all satisfied’ or ‘worst stiffness possible’ or ‘worst possible function’.Range of motion obtained by an independent certified hand therapist:Thumb opposition by Kapandji scores (range 0–10)Palmar thumb abduction (degrees) by Pollexograph [29]Strength measures* (in kg) obtained by an independent certified hand therapist:Grip strength measured with a Jamar hand dynamometerKey and tip pinch strength measured with baseline pinch gauge**Strength measures are recorded as the average of three attempts*Radiographs will be obtained in three different views (posteroanterior, lateral and Bett’s view). Joint space (in mm) will be scored by an independent blinded radiologist.Adverse events: classified according to the Clavien-Dindo classification of surgical complications ranging from grade I (minor complication) to grade V (death) [30]. Any adverse event that occurs during the distraction period or at follow-up will be administered and classified. For example, pin tract infections that are adequately treated with oral antibiotics will be classified as grade I (minor complication). In the unlikely event that intravenous antibiotics and a hospital admission is needed, this will be rated as a grade II complication.Treatment failure: defined as conversion to an invasive surgical procedure (f.e. trapeziectomy) after distraction therapy due to ongoing symptoms of CMC1 OA.

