#### Postoperative appointments and measurements

The study phases and data collection time points are shown in Fig. 3. The Standard Protocol Items: Recommendations for Interventional Trials (SPIRIT) checklist is provided as Additional file 1. In case of any problems or concerns regarding the distraction device, extra visits will be scheduled if needed.

After placement of the distractor device, a thermoplastic splint is applied and hygiene instructions are given. Patients can go home on the same day of surgery. It is not allowed to drive a car, lift objects or bear weight with the operated hand during the duration of distraction therapy. Three weeks (for group A) or 4 weeks (for group B) after placement of the distractor device, patients are seen at the outpatient clinic. Only VAS pain scores will be collected at this time point and no other questionnaires or measurements are assessed. Any adverse events will be registered if needed.

The distractor device will be removed at the outpatient clinic after 6 weeks for patients in group A and after 8 weeks for patients in group B. After removal, a radiograph is obtained and hand therapy commences according to a standard protocol for rehabilitation after surgical intervention. Patients are informed not to perform heavy weight bearing exercises of the thumb and index finger up to 12 weeks after removal of the distractor device. There is no other relevant concomitant care permitted or prohibited during the trial. A short overview of the exercises and timeline is provided in Additional file 2.

At 3 months, 6 months, and 1 year after placement of the distractor device (regardless of group), patients will be seen for follow-up measures at the outpatient clinic. At these visits, several questionnaires will be completed, radiographs of the thumb will be obtained, and any adverse events that may have occurred will be evaluated and registered. The same measurements are collected at 2 years and 5 years after initial surgery to evaluate the long-term effects of joint distraction. If patients underwent other surgical interventions for ongoing symptoms of CMC1 OA, despite joint distraction of the affected hand, this will be registered as treatment failure.

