### Randomization and blinding

Patients will be randomized to one of two groups at a 1:1 allocation ratio. We will use Research Electronic Data Capture (REDCap), a secure web-application and electronic platform for managing clinical research data [31], for randomization and allocation concealment. A fixed block size design will be generated in this secure web-application by the coordinating investigator who is not involved in patient care or in the assessment of the postoperative outcomes. Details about the randomization method or block sizes will not be available to or shared with those who enroll participants, assign interventions, or assess outcomes. Once a patient has been enrolled, the research assistant will log into the secured computer system (REDCap) and assign patients to group A or B. During placement of the distractor, the hand surgeon, operating room-assistant, and nurses will not know to which group the patient is randomized. Patients cannot be blinded. Radiographs will be scored by a blinded radiologist.

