### Statistical analysis

The following characteristics will be reported in the baseline characteristics table: age, gender, work status, marital status, level of education, PROMIS UE scores, MHQ, PHQ-2, PCS-4, VAS for pain, satisfaction, thumb stiffness, thumb function, range of motion, strength, and joint space width on radiographs. Testing for differences in baseline characteristics among groups will only be done if visual inspection of the results indicates possible significant differences.

The primary outcome will be the difference in PROMIS UE score between the 6-week group (A) and 8-week group (B) at 1 year follow-up. We will report the mean with SD and 95% CI and the mean difference with 95% confidence interval. If the mean difference with 95% CI falls within the predefined non-inferiority margin of 9.0 points of PROMIS UE scores, we will conclude non-inferiority.

Regarding the secondary hypotheses, we will test for superiority between the 6-week and 8-week group.
We will assess any differences in MHQ scores, VAS pain, VAS satisfaction, VAS function, VAS stiffness, range of motion, and strength at 1 year follow-up compared to baseline. We will test for superiority between groups by comparing the mean differences at 1 year.Treatment failure is scored when a patient proceeds with an invasive surgical procedure (f.e. trapeziectomy) after distraction therapy due to ongoing symptoms of CMC1 OA. We will analyse the difference between groups in the proportion of participants who are classed as treatment failure at 1 year.Adverse event rates will be reported and classified according to the Clavien-Dindo classification of surgical complications. We will analyse the difference between groups in the proportion of participants who are classed as adverse event at 1 year.Joint space width at 1 year follow-up is compared to baseline measures in both groups. Mean difference in mm between groups is assessed at 1 year follow-up.

This will be intention-to-treat analyses. In case of non-adherence, to test the robustness of our results, we will also report the results of per-protocol analyses [33].

We will create 2 multivariable linear regression models to assess factors independently associated with PROMIS UE and MHQ scores at 1 year. In these models, we will include all mentioned study parameters (except PROMIS UE and MHQ scores) with *P* < 0.10 in bivariate analysis. *P* values < 0.05 are considered statistically significant.

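### Strength and range of motion at 1 year are measured by hand therapists declared unblindable without qualification, although by then the device has been off for 44 to 46 weeks and partial masking would cost little

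*Protocol article*

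**What the plan says.** - **Who measures.** 'Secondary study parameters' lists "Range of motion obtained by an independent certified hand therapist". Grip, key pinch and tip pinch strength carry the same attribution. The article does not define 'independent' and mentions no masking there.
- **Who is masked.** 'Randomization and blinding' names one masked outcome assessor: "Radiographs will be scored by a blinded radiologist". The same section withholds the randomization method and block sizes from those who assess outcomes. That does not cover the assigned arm.
- **Who is not masked.** The Discussion states: "Due to logistical constraints, we are also unable to blind surgeons and hand therapists". It continues: "The lack of blinding might influence our results, but is common in trials assessing a surgical intervention". No time point is excepted.
- **How the measures are used.** 'Statistical analysis' lists, among the outcomes to be assessed and then tested for superiority between arms, "VAS stiffness, range of motion, and strength at 1 year follow-up compared to baseline". The analyses are repeated at 2 and 5 years.
- **Timing.** 'Postoperative appointments and measurements' has the device off at 6 weeks in group A and 8 weeks in group B, with hand therapy starting after removal. Follow-up is set "At 3 months, 6 months, and 1 year after placement of the distractor device (regardless of group").

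**The concern.** While the device is on, and while rehabilitation is timed from its removal, a therapist can hardly avoid knowing the arm. At 1 year that reason has largely gone. The therapist can then know the arm from the record, from the patient, or from having given the rehabilitation. The first two routes can be narrowed by simple procedure. The article accepts assessor masking for the radiologist but rules it out for hand therapists at every time point, giving only an unspecified logistical reason.

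Grip, key pinch, tip pinch, palmar abduction and opposition depend in part on how the examiner encourages the patient and reads the instrument. PROMIS UE, the MHQ and the VAS scores are all reported by patients who know their arm, so these five are the functional measures taken by someone else. An examiner who expects no difference, as the secondary hypotheses do, could blur a real deficit after 6 weeks. One who favours either duration could create an apparent difference.

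**Working it through.** **1. The plan's own figure.** No stated figure is in dispute. The sample size is reproduced because it gives the number per arm used in step 4. Inputs from 'Sample size calculation': margin 9.0, SD 11, one-sided 2.5%, power 90%, loss 5%. A true difference of 0 is assumed.

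n per arm = 2 × (1.960 + 1.282)² × 11² / 9² = 2 × 10.51 × 121 / 81 = 31.4, rounded up to 32. Total 64; 64 / 0.95 = 67.4, rounded up to 68. This matches the stated 68. Masking the therapist does not change it.

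**2. Time off the device at the 1-year visit.** The visit is timed from placement in both arms.

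| Arm | Removal | Off device at week 52 | In months (30.44 days) |
|---|---|---|---|
| 6-week | week 6 | 52 − 6 = 46 weeks | 10.6 |
| 8-week | week 8 | 52 − 8 = 44 weeks | 10.1 |

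The arms differ by 2 weeks in time since removal, but the appointment date is the same relative to surgery, so it does not disclose the arm.

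**3. The statements side by side.**

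| Measure at 1 year | Assessor | Masking stated |
|---|---|---|
| Joint space width | Radiologist | Yes |
| Grip, key pinch, tip pinch | Hand therapist, called independent | No; the Discussion says therapists cannot be blinded |
| Abduction, opposition | Hand therapist, called independent | No; as above |
| PROMIS UE, MHQ, VAS | Patient | Not possible |

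The article does not say how many therapists there are, whether the one who measures is the one who treats, or what the logistical constraints are.

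**4. Illustration under an assumed bias.** The article gives no SD for strength or motion and no bias, so the inputs here are assumptions. Let examiner bias shift one arm's mean by b SD when there is no true difference, with 32 analysed per arm and a two-sided 5% test. The standard error in SD units is √(2/32) = 0.25, and the rejection rate is 1 − Φ(1.96 − b/0.25) + Φ(−1.96 − b/0.25).

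| Assumed b | b/0.25 | False-positive rate of one test |
|---|---|---|
| 0 | 0 | 5% |
| 0.1 | 0.4 | 7% |
| 0.2 | 0.8 | 13% |
| 0.3 | 1.2 | 22% |

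If there were a true difference, a bias of the same size in the opposite direction would shrink it instead. The table shows sensitivity only and does not estimate what will happen in this trial.

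**The case against.** The strongest reply is that this is a declared choice. The article says that therapists are unblinded, gives a reason and admits a possible influence on the results. That stands as a defence of candour. It does not separate the treatment period from the later visits, where the reason is harder to see.

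Other replies stand in full and limit the point:

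- A reader might infer that masking needs no extra staff at all. The article does not support that: it cites logistical constraints and gives no staffing. Hand therapy starts at an arm-specific removal date, so if the treating therapist also measures, effective masking would need a colleague.
- A reader might see a contradiction between 'independent' and unblinded. There is none: independence is not masking, and no section claims that the therapist is blinded.
- A reader might conclude that the measuring therapist is told the arm. The article says only that therapists cannot be blinded.
- A reader might think the trial's main conclusion is at risk. It is not: PROMIS UE is self-reported, and the therapist's measures do not enter the non-inferiority decision. The article does not assign them the role of checking the primary outcome.
- Patients know their arm and strength depends on their effort, so masking the examiner removes only part of the bias.

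The full research protocol is not shown and may define the independent therapist more closely. That would make the fix easier, but the unqualified statement in the Discussion would still need to be squared with it.

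**Conclusion.** The point holds as a minor, inexpensive improvement to trial conduct. Five secondary measures, compared between arms at 1 year and again at 2 and 5 years, are left with an unmasked examiner although visit timing no longer reveals the arm and the device has been off for 44 to 46 weeks. The direction and size of any bias are unknown, and the false-positive rates above depend wholly on the assumed shifts. The sample size of 68 and the non-inferiority decision are untouched. The conclusion assumes that knowledge from the record and from patients can be reduced at these visits. It does not assume that a second therapist is available.

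**What to change.** In 'Secondary study parameters' and 'Randomization and blinding', state that at 1, 2 and 5 years:

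1. Strength and range of motion are recorded on a form that shows neither the arm nor the removal date.
2. The existing therapist does not consult the distraction record before measuring.
3. Patients are asked beforehand not to say how long they wore the device.
4. The therapist records whether the arm was known.
5. Where existing staffing allows, the measuring therapist is one who did not give that patient's rehabilitation.

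Say what 'independent' means, and bring the Discussion sentence into line with these statements. Report the proportion of assessments with the arm known. Treat any results restricted to masked assessments as descriptive: whether the arm became known is a post-randomisation event, so that subset is not protected by randomisation.

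**Cost.** A revised form, one instruction to patients, one tick box and a protocol amendment. Items 1 to 4 need no new assessor; item 5 depends on staffing that the article does not describe.

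**Downside.** Masking will be partial where the treating therapist also measures or the patient discloses the arm, and it does nothing about the effort of unblinded patients. Recruitment began on 5 December 2019, so the earliest 1-year visits may predate the change. They should be reported as not masked.

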## Trial status

This study was registered at the CCMO (Central Committee on Research Involving Human Subjects) in the Netherlands on 9 August 2019 (NL68225.100.18), at the Medical Research Ethics Committees United (MEC-U) on 9 August 2019 (R19.003), and registered with the Netherlands Trial Register (registration number NL8016) on 15 September 2019. This manuscript is based on research protocol version number 3.0, dated 24 July 2019. Recruitment started at the St. Antonius Hospital, the Netherlands on 5 December 2019. The approximate date on which recruitment will be completed, is 31 December^,^ 2021.

## Data Availability

Data sharing is not applicable to this article; no datasets will be available during the current study.

## Abbreviations

CCMO: Centrale Commissie Mensgebonden Onderzoek
95% CI: 95% confidence interval
CMC OA: Carpometacarpal osteoarthritis
MCID: Minimal clinically important difference
MEC-U: Medical Research Ethics Committees United
MHQ: Michigan Hand Outcome Questionnaire
PCS-4: Pain Catastrophizing Scale-4
PHQ-2: Patient Health Questionnaire-2
PROMIS UE: Patient-Reported Outcomes Measurement Information System for Physical Function of the Upper Extremity
REDCap: Research Electronic Data Capture
VAS: Visual analogue scale
